#### Primary endpoint

2.7.1

The cumulative incidence of further decompensation events is defined as any of the following in cirrhotic patients 48 weeks after the first decompensation: (1) Development of a second portal hypertension - driven decompensating event (ascites, variceal bleeding, or hepatic encephalopathy) and/or jaundice; (2) Recurrent variceal bleeding, recurrent ascites (≥3 large-volume paracenteses within 1 year), recurrent encephalopathy, spontaneous bacterial peritonitis (SBP) and/or hepatorenal syndrome - acute kidney injury (HRS-AKI); (3) In patients with bleeding alone, development of ascites, encephalopathy, or jaundice after recovery from bleeding (not during the bleeding episode); (4) After the first decompensation, the new increase of total bilirubin >51.3 μmol/L (3 mg/dL) was judged as jaundice (de Franchis et al., 2022).

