#### Safety assessments

2.7.3

The researchers closely observed the physical condition of the participants and checked them accordingly before enrolling in the group. The investigator will record all adverse events on the case report form (CRF) and report them to the person in charge. At the same time, any serious adverse events will be reported to the ethical committee of Beijing Ditan Hospital within 24 h, and the medical expert committee will determine whether the adverse events are related to FZHY. Participants have the right to withdraw from their consent to participate in the study at any time for any reason. The investigator will record the timing of the adverse event, its severity, the duration of the disease, and the appropriate actions taken in response to the adverse event.

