### Sample size calculation

2.10

Sample size was calculated using a two-sided Z-test for two independent proportions with α = 0.05 and power = 80% (β = 0.20). Based on retrospective data, the 48-week cumulative incidence of further decompensation was 53.7% in patients who received commercial Chinese polyherbal preparation (CCPP) (including Fuzheng Huayu, Anluo Huaxian, or Fufang Biejia) plus antiviral therapy, and 67.5% in patients who received antiviral therapy alone. Applying these proportions to the current prospective trial (Fuzheng Huayu combined with antiviral therapy versus placebo combined with antiviral therapy) with a 1:1 allocation ratio, the required sample size per group was calculated as 194 using the formula. Accounting for a 10% dropout rate, we enrolled 216 patients per group, for a total of 432 patients. The calculation was performed using PASS 2021.
$$n=\frac{\left[{\left(Z_{\left\{\frac{\alpha }{2}\right\}}+Z_{\beta }\right)}^{2}\times \left(p1\left(1-p1\right)+p2\left(1-p2\right)\right)\right]}{{\left(p1-p2\right)}^{2}}$$
where 
$Z_{\left\{\frac{\alpha }{2}\right\}}$
 = 1.96 (for α = 0.05), Z_β_ = 0.842 (for β = 0.20, power = 80%)

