### Data analysis plan

2.11

We used competitive risk analysis to ensure an accurate assessment of the cumulative incidence of specific events, Kaplan-Meier method was used for the survival curves of the two groups, and log-rank method was used for the comparison of the cumulative survival rates of the two groups. Continuous variables will be summarized as mean ± standard deviation or median with interquartile range. Within-group changes from baseline may be assessed using paired t-tests or Wilcoxon signed-rank tests, as appropriate. Between-group comparisons of changes from baseline will be performed using independent-sample t-tests or Wilcoxon rank-sum tests. The notational information of each visit of the two groups will be described statistically using frequency (percentage). Changes in the two groups before and after treatment were analyzed using the chi-square test. All statistical tests will be two-sided, and p < 0.05 will be considered statistically significant for the differences tested. Statistical analyses will be calculated using SPSS and SAS analysis software.

Analysis populations: Defined the ITT population as all randomized participants, analyzed according to their original randomized assignment regardless of whether they received the assigned treatment or completed the study. Defined the per-protocol (PP) population as participants who completed the 48-week treatment period without major protocol violations. In the ITT analysis, if the data related to the efficacy are missing, the method of last observation carried forward (LOCF) will be used to fill in.

Shedding analysis: Comparison of total shedding rate and shedding rate due to adverse events between the two groups will be done using chi-square test.

Balance analysis of baseline values: ANOVA or chi-square test will be used to compare demographic data and other baseline value indicators, and to measure how balanced the two groups are.

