Adherence analysis: Adherence will be calculated as (actual dose taken/prescribed dose) × 100% over the 48-week treatment period. Good adherence is defined as adherence between 80% and 100% (inclusive). Participants with adherence <80% will be classified as having poor adherence. Participants with adherence >100% will be documented as protocol deviations and reviewed for safety; these participants will not be classified as good adherence and will be excluded from the per-protocol population. The chi-square test will be used to compare the proportion of participants with good adherence between the two groups.

Effectiveness analysis: For the primary time-to-event efficacy endpoint, a Cox proportional hazards model will be used to estimate the treatment effect, with treatment group as the main factor and study center included as a stratification factor or covariate, depending on the number of participants and events in each center. The Kaplan-Meier method and log-rank test will be used for descriptive and unadjusted comparisons. For binary efficacy outcomes, logistic regression adjusted for study center and relevant baseline covariates will be used. If some centers enroll only a small number of participants or have few outcome events, centers may be pooled according to prespecified rules before model adjustment.

Safety analysis: the chi-square test was used to compare the incidence of adverse events between the two groups and a list describing the adverse events that occurred in this study; the changes in normal/abnormal laboratory test results before and after the study as well as the relationship with the study drug in the event of abnormal changes.

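### The only between-group test of adverse-event incidence does not separate primary-endpoint events; if those are recorded as adverse events, a benefit on decompensation can mask a drug-caused excess in that test.

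*Protocol article*

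**What the plan says.** All references are to the protocol article.

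- **Test.** The Safety analysis paragraph of section 2.11 says "the chi-square test was used to compare the incidence of adverse events between the two groups". It adds "a list describing the adverse events that occurred in this study", and a description of laboratory changes with their relation to the study drug.
- **Recording.** Section 2.7.3 (Safety assessments) says "The investigator will record all adverse events on the case report form (CRF"). No section exempts events that meet the primary-endpoint definition. The same section says that "the medical expert committee will determine whether the adverse events are related to FZHY".
- **Endpoint.** Section 2.7.1 includes "Development of a second portal hypertension - driven decompensating event (ascites, variceal bleeding, or hepatic encephalopathy) and/or jaundice", and also recurrent bleeding, ascites or encephalopathy, spontaneous bacterial peritonitis and HRS-AKI.
- **Expected frequency.** Section 2.10 takes a 48-week incidence of 53.7% for the Fuzheng Huayu arm and 67.5% for the control arm.
- **Dropout.** Section 2.11 also plans "Comparison of total shedding rate and shedding rate due to adverse events between the two groups will be done using chi-square test".
- **Time.** Treatment lasts 48 weeks (section 2.6). Table 2 schedules AE recording to week 96. The Safety analysis paragraph names no time window.

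**The concern.** Variceal bleeding, new ascites, encephalopathy, jaundice, peritonitis and acute kidney injury are all untoward medical events. An investigator told to record every AE would normally enter them. In this trial they are expected in more than half of each arm, and more often in the control arm if the drug works.

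An any-AE comparison then has two parts: a large one that is the efficacy endpoint again, and a smaller one that carries the information on toxicity. A benefit in the first can offset harm in the second. Safety is a stated aim in the abstract, and AEs are a listed secondary outcome. A finding of no difference, or of fewer AEs on Fuzheng Huayu, could therefore be read as evidence of safety when it reflects efficacy.

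**Working it through.** **1. The plan's own figure.** Section 2.10's formula with p1 = 0.537, p2 = 0.675, z = 1.96 and 0.842:

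n = (2.802)² × (0.537×0.463 + 0.675×0.325) / (0.138)² = 7.851 × 0.4680 / 0.01904 = 192.9, so 193 per group against the stated 194. With 10% dropout, 194/0.9 = 215.6, so 216. The stated figures reproduce to within one patient, and the two rates can be used as the plan's working assumption.

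**2. Size of the overlap.** At 216 per arm, 216 × 0.675 = 146 control and 216 × 0.537 = 116 Fuzheng Huayu patients would have an endpoint event, 262 of 432. At 194 per arm the counts are 131 + 104 = 235.

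**3. Model.** Let d be the endpoint rate and q the rate of other AEs. If every endpoint event is recorded as an AE and the two are independent,

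any-AE incidence = 1 − (1 − d)(1 − q).

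The identity is exact without independence if q is read as the rate among patients free of endpoint events. Independence is what extends it to all patients.

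**4. Excess that cancels exactly.** Equal totals require 1 − q1 = (0.325/0.463)(1 − q0) = 0.7019 (1 − q0), where q0 is the control and q1 the Fuzheng Huayu rate. For q0 = 0.20: 1 − q1 = 0.5616, so q1 = 43.8%. The article gives no q0, so a range is shown. The last column is the power of a two-sided 5% test (normal approximation) on other AEs alone, 216 per arm.

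| q0 (assumed) | q1 | Excess, points | Any-AE, both arms | Power, other AEs only |
|---|---|---|---|---|
| 0% | 29.8% | 29.8 | 67.5% | >99% |
| 20% | 43.8% | 23.8 | 74.0% | >99% |
| 40% | 57.9% | 17.9 | 80.5% | 96% |
| 60% | 71.9% | 11.9 | 87.0% | 75% |
| 80% | 86.0% | 6.0 | 93.5% | 38% |

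In every row the any-AE test rejects only at its 5% level.

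**5. A fixed 15-point excess.**
- 20% vs 35%: totals 74.0% control and 1 − 0.463×0.65 = 69.9% Fuzheng Huayu. The any-AE test has 16% power, and the difference favours the drug. The separated test has 94%.
- 40% vs 55%: totals 80.5% and 79.2%. Power is 6% against 88%.

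**6. Partial recording.** If only a fraction f of endpoint events is entered as AEs, replace d by f×d. For f = 0.5 and q0 = 0.20: 1 − q1 = (0.6625/0.7315) × 0.80 = 0.7245, an excess of 7.5 points. For q0 = 0.40 it is 5.7 points. For f = 0 there is no cancellation.

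**7. No efficacy.** If the endpoint rate is 67.5% in both arms, a 30% vs 45% excess gives totals of 77.3% and 82.1%. The any-AE test has about 24% power, against about 90% for the separated test. This is ordinary dilution, not cancellation, but it shows that the mixed test is also weak when the drug has no effect on the endpoint.

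**The case against.** The strongest reply is that the article is silent rather than wrong. It nowhere says that endpoint events enter the AE test, and such conventions are often set in a full protocol or analysis plan that is not shown. Two places even suggest a separation. Section 2.9 lists serious AEs and severe disease-related complications as different reasons for withdrawal, and section 2.7.2 lists liver failure, hepatocellular carcinoma and liver-related death apart from AEs. This stands as a limit: counting endpoint events as AEs is an inference. But neither place is an exemption, section 2.7.3 asks for all AEs, and the article did choose and state the comparison.

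Second, the test is not the only safety output. The AE list, the committee's judgement on relatedness, the laboratory changes and the comparison of AE-related dropout could each reveal an excess. This also stands, and a reader who infers that toxicity would be hidden goes too far. These outputs do not replace the missing comparison, however. The list is descriptive, and no between-arm test of drug-related AEs is stated. Dropout has the same overlap through section 2.9, and a bilirubin rise above 51.3 μmol/L is itself an endpoint event.

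Third, excluding endpoint events has a cost of its own. Drug-related liver injury or bleeding could appear as jaundice or variceal bleeding and drop out of view. This is a good reason not to make the restricted comparison the sole or main one.

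Finally, one might infer from Table 2 that AEs from weeks 48 to 96 will dilute the test. Table 2 is a visit schedule and does not fix the analysis window, so that reading is not established.

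**Conclusion.** The point holds in conditional form. If endpoint events are recorded as AEs, as the plain reading implies, the stated test is insensitive to a drug-caused excess at the plan's own event rates and can point in the drug's favour. The cancelling excess is about 24 points at a 20% base rate, 18 at 40% and 6 at 80% under full recording. It is about 6 to 8 points under half recording (base rate 40% to 20%), and zero if none are recorded.

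The full-recording figures are a ceiling. They rest on the assumed 67.5% and 53.7%, on independence, and on a base rate that the article does not give. A reader might infer that a large toxicity would go unseen or that the safety conclusion is already compromised. The documents support neither: the base rate and the recording practice are unknown, and the other safety outputs remain. The planned test can mask an excess, and an additional comparison would remedy that cheaply.

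**What to change.** In the Safety analysis paragraph of section 2.11:

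- State whether events meeting the section 2.7.1 definition count as AEs.
- Keep the all-AE comparison. Beside it, with equal prominence, report a between-group comparison of AEs and of serious AEs excluding events that meet that definition, with onset from first dose to week 48.
- Tabulate the endpoint events, including jaundice and bleeding, separately by arm, so that possible drug-related liver injury or bleeding stays visible.
- Show weeks 48 to 96 separately.

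The cost is wording and one extra set of tables. The primary analysis already has to identify endpoint events, and section 2.7.3 already records AE timing. Borderline events, and repeat events after a patient's first, must be classified consistently. The resulting safety figure may look less favourable to the drug than the all-AE figure alone.

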### Trial design and setting

2.3

This is a randomized, double-blind, placebo-controlled, multicenter trial designed to compare the incidence of recurrence of a first decompensation in patients treated with Fuzheng Huayu tablets [4 tablets three times a day] and placebo. Patients will be randomly assigned in a 1:1 ratio to receive either Fuzheng Huayu or placebo. Regular follow-up will be conducted every 12 weeks (Table 2). The flowchart of this trial is shown in Figure 1. Written informed consent was required for all participants before randomization (Supplementary Materials 5, 6). This protocol was prepared in accordance with the Standard Protocol Project, i.e., Recommendations for Intervention Trials (SPIRIT 2025) guidelines (Supplementary Material 7).

**TABLE 2 T2:** The standard process of the form for the plan.

Study period	V1	V2	V3	V4	V5	V6	V7
	(Baseline)						
Study duration (Weeks)	0w	12w	24w	36w	48w	72w	96w
Informed consent Signing​​	●	​	​	​	​	​	​
Medical history taking	●	​	​	​	​	​	​
Physical examination and vital signs	●	●	●	●	●	●	●
Urinalysis	●	○	●	○	●	○	●
Complete blood count	●	●	●	●	●	●	●
Liver fibrosis	●	○	○	○	●	○	●
Liver function	●	●	●	●	●	●	●
Renal function	●	●	●	●	●	●	●
Quantitative hepatitis B surface antigen (HBsAg)	●	○	○	○	●	○	●
Quantitative hepatitis B e antigen (HBeAg)	●	○	○	○	●	○	●
HBV-DNA viral load	●	●	●	●	●	●	●
Coagulation function tests	●	●	●	●	●	●	●
Electrolyte panel	●	●	●	●	●	●	●
Thyroid function tests (TFTs)	●	○	○	○	●	○	●
Serum alpha-fetoprotein (AFP)​​	●	●	●	●	●	●	●
Abdominal ultrasound (US)​​	●	●	●	●	●	●	●
Liver stiffness Measurement (FibroScan)	●	○	●	○	●	●	●
Gastroscopy (for upper gastrointestinal Bleeding)​​	●	●	○	○	●	○	●
Liver biopsy Pathology​​	○	​	​	​	○	​	○
Immune-related biomarkers	●	​	●	​	●	​	●
Adverse events (AEs)	●	●	●	●	●	●	●

“●” indicates items that must be inspected/recorded, and “〇” indicates items that should be inspected/recorded as needed.

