### Withdrawal criteria

2.9

Participants will withdraw from the trial if: (1) the patient has experienced a serious adverse event. (2) Patients with severe changes or complications were associated with the disease during the trial. (3) Patients were unable to comply with the study plan, resulting in incomplete medical management records. (4) Patients who voluntarily requested to withdraw from the trial.

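### Adverse events are compared as crude proportions, while the withdrawal criteria may end observation at disease complications assumed less frequent on FZHY; equal rates of other adverse events could then look like an excess on FZHY

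*Protocol article*

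**What the plan says.** Section 2.11 (Safety analysis) fixes the between-arm method: "the chi-square test was used to compare the incidence of adverse events between the two groups". It adds a listing and laboratory shifts. Dropout due to adverse events is also compared by chi-square. No person-time or time-to-event method is named for safety, although the same section uses Cox, Kaplan-Meier and competing-risk methods elsewhere.

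Section 2.9 lists the reasons for leaving the trial. One is a serious adverse event. Another reads: "Patients with severe changes or complications were associated with the disease during the trial". Both are grounds for withdrawal from the trial, not only from study drug.

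Section 2.7.1 builds the primary endpoint from disease complications such as variceal bleeding, encephalopathy, spontaneous bacterial peritonitis and hepatorenal syndrome.

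Section 2.10 takes from retrospective data that "the 48-week cumulative incidence of further decompensation was 53.7% in patients who received commercial Chinese polyherbal preparation (CCPP" and related preparations) plus antiviral therapy, against "67.5% in patients who received antiviral therapy alone", and applies these figures to the two trial arms. On attrition it says: "Accounting for a 10% dropout rate, we enrolled 216 patients per group, for a total of 432 patients". The 10% is not split by arm.

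Planned treatment (48 weeks), follow-up (96 weeks) and adverse-event visits (Table 2) are the same in both arms. Section 2.7.3 has all adverse events recorded and states no exclusion for endpoint events.

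**The concern.** Comparing the proportions of participants with an adverse event is fair when both arms are observed for similar lengths of time. Read together, sections 2.9, 2.7.1 and 2.10 put that in doubt. If a complication that counts towards the primary endpoint also takes the participant out of the trial, observation ends earlier and more often in the arm with more complications. The plan expects that to be placebo. An adverse event with the same weekly rate in both arms then has more time to appear on FZHY.

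At stake is the safety conclusion. A difference produced only by observation time could be read as toxicity, and the chi-square test would exceed its nominal 5% error. Safety is a stated aim in the Abstract.

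**Working it through.** **The plan's own figure first.** The printed formula gives (1.96 + 0.842)² × (0.537×0.463 + 0.675×0.325) / 0.138² = 192.9, so 193 against the stated 194. Then 194/0.9 = 215.6, so 216 per arm. The inputs are consistent with the stated sample size.

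**Inputs.** 53.7%, 67.5%, 10% dropout and 216 per arm come from section 2.10. The 48 weeks come from sections 2.6 and 2.10. The article does not give the share *q* of primary events that end observation, or any adverse-event rate. Both are assumptions, so a range is shown.

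**Model.** Hazards are constant, and adverse events are independent of decompensation.

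- Weekly decompensation hazard: λ = −ln(1 − p)/48. FZHY: −ln(0.463)/48 = 0.01604. Placebo: −ln(0.325)/48 = 0.02342.
- Share withdrawn by week 48: 1 − (1 − p)^q.
- Mean observation to week 48: (1 − exp(−48qλ))/(qλ).
- Observed incidence of an adverse event with weekly rate *a*: a/(a + qλ) × [1 − exp(−48(a + qλ))]. The same *a* is used in both arms, chosen so that the placebo arm shows 20, 30 or 40%.
- Rejection rate of the two-sided 5% test: normal approximation, 216 per arm.

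**Example, q = 1.** Mean observation is 0.537/0.01604 = 33.5 weeks on FZHY and 0.675/0.02342 = 28.8 weeks on placebo. A placebo incidence of 30% needs a = 0.0133. On FZHY this gives 0.0133/0.02934 × [1 − exp(−1.408)] = 34.2%. The difference of 4.2 points has a standard error of about 4.5 points, and the test rejects about 16% of the time.

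| q | Withdrawn by week 48, FZHY / placebo | Mean weeks, FZHY / placebo | Ratio | FZHY incidence when placebo shows 30% | Rejection at placebo incidence 20 / 30 / 40% |
|---|---|---|---|---|---|
| 0.11 (10% withdrawn on average) | 8.2% / 11.8% | 46.0 / 45.1 | 1.020 | 30.5% | 5.1 / 5.2 / 5.3% |
| 0.25 | 17.5% / 24.5% | 43.7 / 41.8 | 1.043 | 31.2% | 5.5 / 5.9 / 6.2% |
| 0.5 | 32.0% / 43.0% | 39.8 / 36.7 | 1.085 | 32.3% | 7.0 / 8.2 / 9.6% |
| 1 | 53.7% / 67.5% | 33.5 / 28.8 | 1.161 | 34.2% | 11.7 / 15.6 / 19.9% |

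Adverse events are recorded to week 96. If the same hazards continued, the observation ratio would be 1.16 at q = 0.5 and 1.28 at q = 1. The article gives no event rate beyond week 48, so this only illustrates the direction.

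**Opposite direction.** If decompensations count as adverse events, and the risk of any other event is 30% by week 48, any-event incidence is 1 − 0.463×0.70 = 67.6% on FZHY and 1 − 0.325×0.70 = 77.3% on placebo. That is a deficit on FZHY. It is the same whether or not observation ends at decompensation, because the decompensation is then itself the counted event.

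**The case against.** A reader might infer that the sample-size figures by themselves show longer observation on FZHY. They do not. 53.7% and 67.5% are event incidences, no section gives observation time by arm, and the planned schedule is identical. The step to unequal observation needs section 2.9 and an unstated value of q.

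A reader might also take the 16% rejection rate as the error of the planned test. It requires every primary event to end observation, so that 54-68% leave by week 48, against a planned 10%. At 10% the effect is negligible. Other text also points away from q = 1. Section 2.9 speaks of severe complications, while a primary event can be a bilirubin rise or new ascites. The secondary outcomes include liver failure, carcinoma and liver-related death, and follow-up runs to week 96. This stands as a limit on size. It does not remove the conflict: the 10% is a sample-size allowance that the article never squares with section 2.9, and applying that rule to a quarter of primary events would already withdraw 17.5% and 24.5%.

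Nor do the documents support the reading that a more effective drug must look more toxic. That applies at most to adverse events other than the endpoint, and it reverses for the overall count if decompensations are included.

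Crude percentages are conventional, and an analysis plan that is not shown may add exposure-adjusted rates. But the chi-square comparison is a stated choice, so it can be reviewed as stated. Finally, person-time rates assume that the end of observation is unrelated to adverse-event risk. Withdrawal for deterioration or a serious adverse event may breach this, so the remedy is partial.

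**Conclusion.** The concern holds conditionally. The stated safety comparison ignores observation time, and the withdrawal criteria, followed as written, can make observation time differ between arms because they overlap the primary endpoint. Any resulting bias would be against FZHY and confined to non-endpoint adverse events. It ranges from negligible at the planned dropout to a rejection rate of 12-20% in the extreme case where every primary event ends observation. With a quarter to a half of primary events ending observation, it is 5.5-10%.

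These sizes rest on the retrospective event rates being realised, on constant and independent hazards, on 216 per arm, and on a control incidence of 20-40%. The direction for the overall adverse-event count is not established, because the article does not say whether decompensations are included. The crude test is therefore hard to interpret either way.

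**What to change.** In section 2.11, exclude primary-endpoint events from the main adverse-event comparison and show them separately. Report the remaining events as rates per patient-year of observation with a rate ratio and 95% confidence interval, or as time to first event with death as a competing event. Keep the crude percentages alongside.

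Reconcile sections 2.9, 2.10 and 2.11 so that they say the same thing about whether adverse-event recording continues after further decompensation, and whether the 10% allowance includes withdrawals for disease complications.

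The cost is a few sentences and a little more analysis. Each participant's end-of-observation date is needed; the article mentions the assignment date and the timing and duration of events, but not this date, so its capture should be confirmed. The rates assume a roughly constant hazard and a non-informative end of observation, and both should be stated. If observation proves equal in the two arms, the rate and crude comparisons should broadly agree, so little is lost.

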### Participant selection

2.4

Participants who meet the following selection criteria will be included in the study: (1) voluntarily joining the group, able to understand and sign informed consent forms; (2) age range: 18–80 years old, gender not limited; (3) HBsAg positive for ≥6 months during screening; (4) complies with traditional Chinese medicine syndrome types: blood stasis obstructing collaterals, liver and kidney deficiency syndrome; (5) the first decompensated event, which meets the diagnostic criteria for decompensated cirrhosis in the “Diagnosis and Treatment Guidelines for Cirrhosis (2019 Edition)”: (a) having diagnostic evidence for cirrhosis; (b) complications related to portal hypertension may occur, such as ascites, esophageal and gastric variceal bleeding, hepatic encephalopathy, hepatorenal syndrome, etc.

We will exclude patients who meet any of the following criteria: (1) merge hepatitis A, C, D, E, and/or HIV infections; (2) merge autoimmune liver disease, alcoholic liver disease, drug-induced liver disease and other liver diseases; (3) patients with combined malignant tumors; (4) history of splenectomy and transjugular intrahepatic portosystemic shunt surgery; (5) individuals with neurological and psychiatric disorders, especially those with a history of depression, anxiety, mania, schizophrenia, or a family history of mental illness (especially those with a history of depression or tendencies towards depression); (6) individuals with severe heart, lung, kidney and other organ disorders; (7) individuals who plan to undergo organ transplantation or have already undergone organ transplantation; (8) pregnant or lactating women or those with fertility plans during the study period; (9) for those who are allergic to tonifying the body and removing blood stasis, nucleoside (acid) analogues, or drugs, or who meet any contraindications in the research drug instructions (10) individuals who have taken traditional Chinese medicine such as Fuzheng Huayu within the past 6 months (11) other situations that have participated in other intervention studies within the previous 3 months or are deemed unsuitable for inclusion by the researchers.

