### Intervention

2.6

Fuzheng Huayu group: Fuzheng Huayu 3 times a day, 4 tablets each time for 48 weeks. Conventional western medical treatment: symptomatic supportive therapy + antiviral therapy (recommended first-line potent low-resistance nucleoside (acid) analog therapy: entecavir (ETV)/tenofovir disoproxil (TDF)/propafenacort tenofovir (TAF)/emetinofovir (TMF).

Placebo group: in dosage form, shape, color, texture, odor, and dosage, exactly the same as the study drug, but without the active ingredient of the drug, 4 tablets 3 times a day for 48 weeks of treatment. Conventional western medical treatment: symptomatic supportive therapy + antiviral therapy (recommended first-line potent low-resistance nucleoside (acid) analog therapy: entecavir (ETV)/tenofovir disoproxil (TDF)/propafenacortinofovir (TAF)/emetinofovir (TMF).

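### The only laboratory-specific safety analysis in section 2.11 is a normal/abnormal before-and-after summary, which is insensitive to worsening from an abnormal baseline and names no on-treatment visit

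*Protocol article*

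**What the plan says.** The safety paragraph of section 2.11 (Data analysis plan) has two parts. For adverse events, "the chi-square test was used to compare the incidence of adverse events between the two groups and a list describing the adverse events". For laboratory data it looks at "the changes in normal/abnormal laboratory test results before and after the study as well as the relationship with the study drug" where a change is abnormal. No other sentence in the article is specific to laboratory safety.

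The surrounding text matters for reading that rule:

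- **Schedule (section 2.3, Table 2).** The row "Liver function" and the rows for renal function, coagulation, electrolytes and blood count carry a filled circle at all seven visits (weeks 0, 12, 24, 36, 48, 72, 96). The filled circle "indicates items that must be inspected/recorded".
- **Treatment (section 2.6).** "Fuzheng Huayu 3 times a day, 4 tablets each time for 48 weeks"; placebo runs for the same time. Follow-up continues to week 96.
- **Population (section 2.4).** Entry requires "the first decompensated event, which meets the diagnostic criteria for decompensated cirrhosis".
- **General rules (section 2.11).** For continuous variables, "Between-group comparisons of changes from baseline will be performed using independent-sample t-tests or Wilcoxon rank-sum tests". Categorical data are described by frequency and percentage at each visit.
- **Withdrawal (section 2.9).** A serious adverse event, or severe changes or complications of the disease, are grounds for leaving the trial.

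**The concern.** The rule fits this population and schedule poorly in three ways.

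1. **Abnormal baselines.** A two-category summary records a harm only when a patient crosses from normal to abnormal. In decompensated cirrhosis, bilirubin, albumin, INR or platelets may already be out of range at entry. A patient whose abnormal value then worsens markedly stays in the same category.
2. **Timing.** The rule contrasts one value before with one value after and names none of the on-treatment visits. If the later value is the week 96 one, it is taken 48 weeks after treatment ends, and a rise at weeks 12 to 36 that has resolved leaves no trace in this summary.
3. **Early leavers.** Patients who withdraw under section 2.9 may have no later value. They are also the patients in whom toxicity is most likely. Last observation carried forward is specified only for missing efficacy data, so no rule is given for them here.

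The safety of the added product is a stated aim (Abstract), and the Discussion anticipates describing it as safe. A finding of no difference on this summary would be weak support for that.

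**Working it through.** **The plan's figures.** The plan gives no figure for laboratory safety. Its sample size supplies the denominators. The formula printed in section 2.10 gives (1.96 + 0.842)² × (0.537 × 0.463 + 0.675 × 0.325) / 0.138² = 192.9, that is 193 against the stated 194. Then 194 / 0.90 = 215.6, that is 216 per arm, as stated. Nothing in this point depends on the difference of one.

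**Step 1: panels the rule uses.** From Table 2 there are 6 post-baseline panels (weeks 12, 24, 36, 48, 72, 96), of which 4 fall within the 48-week treatment period (weeks 12, 24, 36, 48).

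- If the later value is week 96: 1 of 6 post-baseline panels is used, and 0 of 4 on-treatment panels.
- If the later value is week 48: 1 of 6 is used, and 1 of 4 on-treatment panels.

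The text does not settle which applies. The safety sentence refers to the study, while an earlier sentence in section 2.11 refers to before and after treatment.

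**Step 2: how many patients can register a new abnormality.** The documents do not give the share *a* abnormal at baseline, so it is assumed and varied. The number able to shift per arm is 216 × (1 − *a*). Power is shown for an assumed 20% against 10% rate of new abnormality, two-sided α = 0.05, normal approximation: Φ{[0.10 − 1.96 √(2 × 0.15 × 0.85 / n)] / √[(0.20 × 0.80 + 0.10 × 0.90) / n]}.

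| Share abnormal at baseline (assumed) | Able to shift, per arm | Power |
|---|---|---|
| 0% | 216 | 83% |
| 30% | 151 | 68% |
| 50% | 108 | 54% |
| 70% | 65 | 36% |
| 90% | 22 | 15% |

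The share will differ by test. Section 2.4 excludes severe kidney disorders, so the high end fits renal tests poorly.

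**Step 3: the transient case.** Suppose 10% on drug and 3% on placebo have a marked rise at weeks 12 to 36 that resolves (assumed). A contrast of baseline with one later value shows an excess of 0, by construction. Comparing worst on-treatment values at 216 per arm: standard error √[(0.10 × 0.90 + 0.03 × 0.97) / 216] = 0.0235; 0.07 / 0.0235 − 1.96 = 1.02; power about 85%. At 194 per arm, after the plan's 10% dropout, it is about 81%.

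Steps 2 and 3 show how the summary behaves. They do not estimate what will happen in this trial.

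**The case against.** A reader might go further and infer that liver, kidney or coagulation toxicity would be missed by the trial, that on-treatment results are discarded, and that abnormalities leading to a patient stopping do not count. The documents do not support this.

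- Section 2.7.3 has all adverse events recorded with timing, severity, duration and action taken, and section 2.11 compares their incidence between arms. A laboratory change reported as an adverse event at week 24 counts even if it resolves.
- Section 2.11 also compares between arms the dropout rate due to adverse events, so harms that lead to withdrawal as adverse events are counted there.
- The general rules for numeric change from baseline and for description at each visit are not limited to efficacy. Bilirubin, INR and creatinine are continuous, so worsening from an abnormal start can show in a numeric comparison.
- The primary endpoint (section 2.7.1) counts a new bilirubin rise above 51.3 μmol/L and hepatorenal syndrome with acute kidney injury.
- Week 96 as the later value is only one reading.
- Worst-value and graded shift tables commonly belong in a statistical analysis plan, which is not shown, so their absence is not itself a fault.

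Most of this stands, and it limits the consequence. It does not rescue the rule as written. The general change-from-baseline tests name no visit or safety variable, and a comparison of means or ranks can pass over a minority who worsen sharply. Section 2.7.2 frames laboratory markers as improvement. The article does not say when a laboratory change becomes an adverse event. The primary endpoint does not count a rise in transaminases, INR or creatinine, or a fall in platelets, as such. The criticism is of a rule the article states, not of one it leaves out.

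**Conclusion.** The point holds in limited form. The one laboratory-specific safety analysis stated is a two-category before-and-after summary. It is insensitive to worsening in patients already abnormal at entry, names no on-treatment visit, and leaves open whether its later value is at week 48 or week 96. Laboratory toxicity that is neither reported as an adverse event nor counted in the primary endpoint could be missed by this analysis. That is narrower than saying the trial would miss it.

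That the summary cannot register such worsening follows from the text. How much it matters rests on assumed values (baseline abnormality of 30% to 90%, new abnormality of 20% against 10%, transient rises of 10% against 3%), none of which the documents give. The change is worth making because it is cheap. It does not touch data collection, sample size, alpha or the primary analysis.

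**What to change.** In the safety paragraph of section 2.11, replace or supplement the before-and-after rule as follows:

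- For each safety test that Table 2 makes mandatory at every visit, compare between arms the worst value from first dose to week 48 relative to the patient's own baseline, as a shift in severity grade or a multiple of baseline.
- Include whatever on-treatment values exist for patients who withdraw early.
- Tabulate weeks 72 and 96 separately as post-treatment.

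The detail can sit in the statistical analysis plan, provided section 2.11 no longer presents the two-category contrast as the only laboratory analysis. Settle the wording before unblinding, so that the choice of summaries cannot be called post hoc.

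The cost is wording and additional tables. With several tests compared, some differences will arise by chance and should be read accordingly. No new visits, samples or patients are needed, because the scheduled values are already collected.
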